Based on the context outlined and considering that there is insufficient evidence using a physiotherapeutic intervention protocol associated with Kangaroo Position in neonatal units, some questions arise: a) Is the combination of a physiotherapeutic protocol with Kangaroo Position more effective in improving clinical outcomes, including body weight, breastfeeding, behavioral state, length of hospital stay? b) Is the combination of a physiotherapeutic protocol with Kangaroo Position more effective in improving posture and tone, and normalizing general movements, in newborns with poor motor repertoire than Kangaroo Position alone?

Considering the evidence that early intervention (SYMINGTON; PINELLI, 2016) and Kangaroo Position (NUNES et al., 2017) improve self-regulation and the mother-infant bond, it is hypothesized that the application of the physiotherapeutic intervention protocol associated with Kangaroo Position over fifteen days in stable preterm newborns hospitalized in a neonatal unit will lead to an improvement in clinical outcomes while safely maintaining vital signs. As a consequence, and based on the beneficial effects of Kangaroo Position (SANTOS; FILHO, 2016) and early intervention (MARLOW, 2004) on body posture, muscle tone, and spontaneous movement, it is expected that these newborns will show better motor patterns immediately after the protocol, and at 12 weeks post-term, compared to control newborns.

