##### *4.8.4.1. Assessments at the UCIN*

The preterm newborns in both the experimental and control groups will be evaluated by the researcher in the NICU regarding respiratory discomfort at two time-points: I) before the

start of the protocol (experimental or control), with the baby still in the incubator/crib (Day 1); and II) after the completion of the protocol with the baby positioned in the incubator/crib (Day 15).

Physiological parameters (heart rate, respiratory rate, peripheral oxygen saturation, body temperature) and behavioral state will be assessed at three-time points daily: I) immediately before the protocol (experimental or control), with the baby still in the incubator/crib; II) 60 minutes after the start of the kangaroo position (experimental or control), while the baby remains in the position; and III) 30 minutes following, with the baby repositioned in the incubator/crib.

GMs and neuromotor screening (posture and tone) will be evaluated at two time-points: I) one day before the start of the protocol; and II) one day after the completion of the protocol.

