#### **4.9.2 Secondary outcomes**

- **Posture and Muscle Tone:** behavior regarding posture and muscle tone, assessed by the classification achieved using the neurological signs evaluation method from the neonatal neuromotor screening (GONÇALVES, 2012).
- **Behavioral State:** Behavioral state according to the adapted Brazelton scale (BRAZELTON et al., 1976).

- **Time to Establish Breastfeeding:** defined as the interval in days between the start of the protocol and successful breastfeeding at the breast. Success in breastfeeding will be considered according to the main key points for proper positioning and latch during the feeding: the baby's face facing the breast, with the nose at nipple level, the baby's body close to the mother's, with the baby's head and torso aligned; the baby well supported; more areola visible above the baby's mouth; mouth wide open; lower lip turned outward; and the chin touching the breast (BRASIL, 2011a).
- **Exclusive Breastfeeding Maintenance:** defined as the continuation of exclusive breastfeeding at corrected ages of 2 weeks post-term, 12 weeks post-term, and at 6 months, being dichotomous.
- **Hospitalization Time:** defined as the average number of days the newborn stays in the hospital environment.
- **Degree of Respiratory Distress** obtained by summing the score according to the BSA (SILVERMAN; ANDERSEN, 1956; BRASIL, 2011b) on each day of the protocol.
- **Physiological Parameters** (heart rate, respiratory rate, peripheral oxygen saturation, body temperature): vital signs evaluated and recorded before and after the protocol (experimental and control) each day.

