#### 4.10 Data Analysis

For the statistical analysis of the data, the statistical package SPSS 23.0 will be used. To analyze the dependent variables, the Levene's Test for Homogeneity of Variance and the Shapiro–Wilk Test for Normality will be applied. Once the assumptions are met, parametric and non-parametric tests may be applied depending on the homogeneity and normality conditions of the sample. Descriptive statistics will first be performed to characterize the sample. Treatment effects will be obtained by comparing the groups

To test differences between groups (treatment effects) for categorical variables (quality of GMs, behavioral state, success, and maintenance of breastfeeding), the chi-square test will be applied. To test differences between groups concerning body weight, the independent t-test will be used. For other continuous variables, t-tests or the Mann–Whitney test will be used to calculate differences between the groups. Adjusted means and 95% confidence intervals may also be calculated using the mixed linear model (GLM) for continuous variables, considering the interaction terms of group x days of evaluation.

To calculate the effect size of the intervention, a 95% confidence interval will be adopted, and either Cohen's d or r ( $r = \text{z-score} / \sqrt{\text{total sample}}$ ) will be considered, depending

on whether parametric or non-parametric tests are used. A significance level of  $\alpha=5\%$  will be considered for all analyses.

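### All secondary outcomes are tested at 5% without a supportive label, while the hypothesis folds several into one claim of better clinical outcomes; vital signs have no named contrast

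*Protocol*

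**What the plan says.** Section 4.10 (Data Analysis) fixes a single significance level: 5% "will be considered for all analyses". It assigns tests by type of variable. For "categorical variables (quality of GMs, behavioral state, success, and maintenance of breastfeeding), the chi-square test will be applied". Body weight has an independent t-test. For the rest, "For other continuous variables, t-tests or the Mann–Whitney test will be used to calculate differences between the groups". A mixed linear model with a group-by-days term is mentioned only as something that may be done in addition.

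Section 4.9.2 lists seven secondary outcomes: posture and muscle tone, behavioural state, time to establish breastfeeding, exclusive breastfeeding at three ages, hospital stay, respiratory distress and four physiological parameters. Nothing in the protocol ranks them or calls their tests supportive, exploratory or descriptive. The only ranking is the split between 4.9.1 and 4.9.2.

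The Introduction asks whether the combination is "more effective in improving clinical outcomes, including body weight, breastfeeding, behavioral state, length of hospital stay". Its hypothesis is that the intervention "will lead to an improvement in clinical outcomes while safely maintaining vital signs".

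Vital signs and behavioural state "will be assessed at three-time points daily" (section 4.8.4.1). Section 4.9.2 describes the physiological outcome as "vital signs evaluated and recorded before and after the protocol (experimental and control) each day". The protocol period is ten days in the Abstract and in 3.1, but fifteen in the Introduction's hypothesis and in 4.8.5.2. These passages must be reconciled.

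**The concern.** Two separate problems meet in section 4.10.

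The first is what may be claimed. Unadjusted 5% tests of secondary outcomes do little harm if no conclusion rests on them. Here the Introduction poses improved clinical outcomes as one effectiveness question. Three of the four items it names are secondary, and no rule says which one, or how many, must succeed. Nothing in the plan would stop a single significant result, such as a shorter stay, from being written up as support for the hypothesis. Section 2 says the results may support implementing the protocol, and section 4 (Relevance) speaks of a model for other hospitals, so such a report would carry weight.

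The second is the vital-sign analysis. Four signs are measured several times a day over many days, but the committed tests compare two groups on a single value per infant. The plan does not say which day, reading or summary supplies that value. The method that could use all readings and return one answer per sign is optional. The statement that vital signs were safely maintained could then depend on which comparison is picked after the data are seen.

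**Working it through.** The plan gives no family-wise figure to reproduce. It states only a per-test level of 5%. I take tests as two-sided, since sidedness is not stated.

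**Step 1. Count the secondary tests (4.9.2), with one test per component as the minimum.**

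- Posture and muscle tone ("behavior regarding posture and muscle tone, assessed by the classification achieved"): 1
- Behavioural state: 1
- Time to establish breastfeeding: 1
- Exclusive breastfeeding at 2 weeks post-term, 12 weeks post-term and 6 months: 3
- Hospital stay: 1
- Respiratory distress score: 1
- Heart rate, respiratory rate, oxygen saturation, temperature: 4

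Total: 1 + 1 + 1 + 3 + 1 + 1 + 4 = 12. The hypothesis treats vital signs as something to be safely maintained, so the count relevant to an efficacy claim is 12 − 4 = 8.

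The 12 is not a hard floor. Section 4.8.4 schedules exclusive breastfeeding after discharge only at 12 weeks post-term. If that is the only age collected, the counts are 10 and 6.

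**Step 2. Chance of at least one false positive when there is no effect.**

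Independent tests, either direction: 1 − 0.95^k. Only results favouring treatment (2.5% each): 1 − 0.975^k.

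- k = 8: 1 − 0.95^8 = 0.337; 1 − 0.975^8 = 0.183
- k = 12: 1 − 0.95^12 = 0.460; 1 − 0.975^12 = 0.262

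For a common correlation r between test statistics, with c = 1.96, the either-direction probability is 1 − ∫ φ(u)·[Φ((c − √r·u)/√(1 − r)) − Φ((−c − √r·u)/√(1 − r))]^k du. The favourable-only version drops the second Φ term.

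| Tests | Direction | r = 0 | r = 0.5 | r = 0.8 |
|---|---|---|---|---|
| 8 (no vital signs) | either | 34% | 25% | 16% |
| 8 (no vital signs) | favours treatment | 18% | 13% | 8% |
| 10 (breastfeeding at one age) | either | 40% | 29% | 17% |
| 12 (all) | either | 46% | 32% | 19% |

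With 6 tests (no vital signs, breastfeeding at one age), the independent figures are 1 − 0.95^6 = 26% in either direction and 1 − 0.975^6 = 14% favouring treatment.

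The correlations are assumptions, because the protocol gives none.

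**Step 3. Vital signs.** Section 4.8.4.1 gives three readings a day: before the session, 60 minutes into kangaroo positioning, and 30 minutes after that. Two of them follow the start of the session. If each were tested separately, there would be 4 signs × 2 readings × 10 days = 80 tests, or 4 × 2 × 15 = 120. The expected number of chance differences is 80 × 0.05 = 4, or 120 × 0.05 = 6, whatever the correlation. This shows what an open choice of contrast permits; it does not describe an analysis the protocol commits to.

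**The case against.** The strongest reply is that this is ordinary practice. The outcomes are headed secondary, the sample size in 4.2 rests on general movements alone, and many trials test secondaries at 5% without adjustment. Labelling and ordering them is often left to a statistical analysis plan, which may exist here. The question and hypothesis are Introduction text. Section 4.10 already asks for effect sizes with a 95% confidence interval. Much of this stands and keeps the severity modest. It does not remove the point: the protocol itself fixes the blanket 5% rule and itself puts secondary outcomes inside the effectiveness claim.

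Four stronger readings are tempting and are not supported.

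- A reader might infer that a spurious secondary finding is likely. For the countable tests the probability is 46% at most, and a false positive against treatment cannot be claimed as benefit.
- A reader might infer that one significant secondary would answer the question even if both primaries failed. No passage says so. The text merely fails to rule it out, and body weight, a primary outcome, heads the list.
- A reader might infer that 80 to 120 vital-sign tests are planned. Section 4.10 does not say that readings will be tested one by one.
- A reader might compare the family-wise figures with the stated 5% as if it had been exceeded. That 5% is a per-test level; the protocol promises no family-wise level.

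**Conclusion.** The point holds in a limited form. Section 4.10 and the Introduction together leave room for a chance secondary result to be reported as efficacy. On the 8 non-safety tests that chance is about 8 to 18% for a result favouring treatment, and 16 to 34% in either direction; all 12 tests give 19 to 46% in either direction. These ranges assume no effect, two-sided tests, one test per component, three breastfeeding ages, and a common correlation between 0.8 and 0. Fewer breastfeeding ages would lower them, and repeated testing of daily measures would raise them.

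The vital-sign gap needs no probability to stand: the committed tests name no contrast for repeated readings, and the better-suited model is optional. Severity is modest, because the outcomes are already headed secondary and wording alone resolves both parts.

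**What to change.** In section 4.10:

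1. State that the outcomes in 4.9.2 are supportive, are reported with an estimate and 95% confidence interval, and that no efficacy claim rests on a secondary p-value. Reword the Introduction's hypothesis on clinical outcomes to match.
2. Make the mixed model already named the committed analysis for each vital sign, in place of the t-test or Mann–Whitney choice. Use infant as random effect, the day-1 pre-protocol reading as covariate, and one group contrast averaged over protocol days. Name which daily readings form the response, since 4.8.4.1 gives three a day and 4.9.2 speaks only of before and after. Keep the group-by-days term as a secondary look, and use day-by-day comparisons for display only.

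The covariate should not be each day's pre-session reading. From day 2 that reading follows randomisation and earlier sessions, so adjusting for it could hide a cumulative effect, including an adverse one.

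The stated lengths of the protocol period must be reconciled so that the averaging window is defined.

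The cost is wording only, with no new data, staff or infants. The downside is that an isolated significant secondary result can no longer be presented as proof of benefit.

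### Vital signs: 4.10 names no use for the daily pre-session reading and does not say whether raw values or changes are tested; adjusting for the day-1 reading would sharpen the comparison at no cost

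*Protocol*

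**What the plan says.** Protocol section 4.8.4.1 states that the four physiological parameters and behavioural state "will be assessed at three-time points daily": reading I just before the session, in the incubator or crib; reading II "60 minutes after the start of the kangaroo position"; and reading III 30 minutes later, back in the incubator or crib. Section 4.9.2 lists the outcome as "vital signs evaluated and recorded before and after the protocol (experimental and control) each day".

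Section 4.10 gives body weight its own t-test and then says: "For other continuous variables, t-tests or the Mann–Whitney test will be used to calculate differences between the groups". It adds that "Adjusted means and 95% confidence intervals may also be calculated" from a mixed linear model, "considering the interaction terms of group x days of evaluation". It does not say what those means are adjusted for. No change score, pre-session covariate or within-session time factor is named.

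The hypothesis in section 1 is that the intervention "will lead to an improvement in clinical outcomes while safely maintaining vital signs".

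**The concern.** A pre-session reading on every infant is the natural tool for removing stable differences between infants from a comparison of later readings. The protocol collects it daily and then gives it no stated role. Section 4.10 does choose a test and an interaction term, so the question is whether those choices suit the data.

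The one interaction it names, group by day, is zero for a reaction of the same size in every session. A group main effect in that model would catch such a reaction. Without a pre-session covariate, though, it would carry the same between-infant error as the t-test.

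At stake is how a null result is read. Because the hypothesis is that vital signs stay safe, a non-significant difference with a wide interval could be taken as reassurance. Overt reactions in single infants are handled at the bedside: section 5 (Risks and Benefits) interrupts handling on signs of overload, and section 4.4 excludes infants with clinical instability. What is left to the analysis is a small or moderate shift in the arm average at readings II and III. No reading is taken during the 15 minutes of handling, so no analysis covers that interval.

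**Working it through.** **The plan's own figure.** Section 4.2 gives 13 per group for a 50-point difference in general-movement quality (80% power, α = 5%), raised to 17. The two rates are not given. The pooled chi-square formula yields 14 for 0.60 v 0.10, 15 for 0.75 v 0.25, 12 for 0.95 v 0.45 and 11 for 1.0 v 0.5, so 13 is reproduced to within two. With an assumed 20% loss, 13/0.80 = 16.25, which rounds up to 17. No sample size is stated for vital signs.

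**Raw values, 17 per arm.** Take the SD of the infants' values as 1 and the test as two-sided at 5%.
- 95% half-width = t(0.975; 32 df) × √(2/17) = 2.037 × 0.343 = 0.70 SD.
- Power (noncentral t, noncentrality d√(17/2)): 14% at d = 0.3, 29% at d = 0.5, 62% at d = 0.8. It reaches 80% only at d = 0.99.
- With 13 per arm: 11%, 23% and 50%; half-width 0.81 SD.

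**ANCOVA on the day-1 reading I.** The residual SD is √(1 − r²), where r is the correlation between that reading and the infant's mean later reading. One degree of freedom is lost. The protocol does not give r, so a range is shown for d = 0.5 (simulation, 20,000 runs):

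| r | Residual SD | Power | Interval width relative to raw |
|---|---|---|---|
| 0 | 1.00 | 29% | 1.02 |
| 0.2 | 0.98 | 30% | 1.00 |
| 0.5 | 0.87 | 36% | 0.88 |
| 0.7 | 0.71 | 50% | 0.73 |
| 0.8 | 0.60 | 64% | 0.61 |

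**Illustration in heart-rate units.** The protocol gives no SDs. Assume a between-infant SD of 10, day SD of 6 and reading SD of 8 bpm, a 5 bpm effect at reading II, and 10 days. (The abstract and section 3.1 say 10 days and section 4.8.5.2 says 15; the results barely differ.) If every infant responds alike:
- Variance of an infant's mean reading II = 100 + 36/10 + 64/10 = 110, so SD = 10.5 and d = 5/10.5 = 0.48. Power is 27%.
- Correlation with the day-1 reading I = (100 + 36/10)/√(200 × 110) = 103.6/148.3 = 0.70.
- Variance of the mean change (II minus I) = 2 × 64/10 = 12.8, so SD = 3.58 and d = 5/3.58 = 1.40. Power is 98%.

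If the response varies between infants with SD R, R² is added to the first and third variances:

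| R (bpm) | Raw mean II: power, half-width | ANCOVA: power, half-width | Change, no carry-over | Change, 50% carry-over | Change, 80% carry-over |
|---|---|---|---|---|---|
| 0 | 27%, 7.3 | 46%, 5.3 | 98% | 59% | 20% |
| 3 | 25%, 7.6 | 41%, 5.7 | 86% | 38% | 14% |
| 5 | 23%, 8.1 | 34%, 6.4 | 63% | 24% | 10% |
| 8 | 19%, 9.1 | 25%, 7.7 | 37% | 14% | 7% |

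Carry-over means that the stated share of the shift is still present in reading I from day 2 on. At 80%, reading I is raised on average by 0.8 × 5 × 9/10 = 3.6 bpm, so the change estimate is 5 − 3.6 = 1.4 bpm. The day-1 reading I precedes all treatment, so ANCOVA on it is not affected in this way.

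For 10 bpm, power is 77%, 73%, 68% and 57% with raw values against 96%, 93%, 87% and 72% with ANCOVA. Across five assumed SD sets and the four values of R, power for 5 bpm ran from 15% to 55% raw and from 20% to 70% with ANCOVA. ANCOVA was higher in all 20 combinations, by as little as 2 points. With no true effect, all three methods rejected in about 5% of runs.

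**The case against.** The strongest reply is that 4.10 does not exclude the pre-session reading. It never says which quantity enters the test. Since 4.9.2 speaks of values before and after each session, a t-test on the change fits the two sections read together. With no carry-over, that test beats the proposed ANCOVA at every R in the table, and at 50% carry-over with R = 0 it still does (59% v 46%). The optional adjusted means could also include a pre-session term. This stands. A reader might infer that 4.10 discards the reading, or that its test has low power as it is written; the text supports neither. Low power follows only if raw values are compared.

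It can also be said that covariates for a secondary outcome belong in a statistical analysis plan, that 4.10 promises a 95% interval with the effect size so imprecision would show, and that ANCOVA with 34 infants remains weak. The first carries limited weight here: 4.10 already picks the test and the model term, and a better choice needs no new data. The second lessens the risk of false reassurance. The third stands: after the change, power for 5 bpm in the illustration is still only 25% to 46%. In a least favourable case (SDs 6/6/8, R = 8, response correlated −0.5 with the infant's level) ANCOVA gains nothing, 44% against 44%.

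**Conclusion.** The point holds as an improvement to consider. The pre-session reading is collected daily, 4.10 names no use for it, and the tested quantity is left open. Each reading of 4.10 has a weakness: raw values give a valid comparison with 29% power at 0.5 SD and an interval of about ±0.70 SD, while changes may be more precise but understate a reaction that persists. ANCOVA on the day-1 reading avoids the second weakness and reduces the first to the extent that r allows.

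The size of the gain rests on r and on SDs that the protocol does not supply. Below r of about 0.2 there is nothing to gain, at the price of an interval at most 2% wider. It would go too far to infer that the planned test is invalid or that adjustment would make the trial adequate for judging vital-sign safety. Randomisation protects the test, larger reactions are more readily detected, and the number of infants was set for general movements. With or without the change, a non-significant result must not be read as proof of safety. The point concerns four secondary outcomes at readings II and III only.

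**What to change.** In 4.10, state for heart rate, respiratory rate, oxygen saturation and temperature:
- The arms are compared on each infant's mean reading II and mean reading III over sessions, by ANCOVA adjusted for that infant's day-1 pre-session reading (on ranks if residuals are clearly non-normal). That is the only pre-session reading treatment cannot affect.
- The within-session change (II minus I and III minus I, averaged over sessions) is reported alongside as the estimate of the acute reaction, with reading I shown by arm and day to reveal carry-over.
- Differences are given with 95% intervals as estimates. Four signs at two readings make eight comparisons; if independent and each tested at 5%, the chance of at least one false positive would be 1 − 0.95⁸ = 34%.
- Group by day may stay as a check for drift over the course.

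The cost is two or three sentences and slightly more reporting. The data and software are the same, and no infants or readings are added.

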## 5. Risks and Benefits

This study presents no physical or psychological risks to the newborn; however, there may be signs of sensory overload such as: color fluctuations (paleness, perioral cyanosis, among others), cardiorespiratory changes (bradycardia, irregular breathing, apnea, irregular respiratory rate), changes in state (hiccups, yawning, salivation, startles, crying, irritability), and signs of withdrawal when the newborn is handled. If signs of overload are detected, the handling should be interrupted to allow the newborn to organize, using maneuvers such as positioning and firm touch.

As for the benefits, the research will provide early stimulation/intervention to hospitalized preterm newborns, enhancing the baby's interaction with the environment through sensory-motor stimuli, which the baby interprets as pleasurable (approach signals). The kangaroo position is a safe and low-cost intervention, which can be performed in any hospital and provides the multidisciplinary team with an important additional resource in the care and attention of preterm newborns and their families, making them active participants in the treatment and promoting an efficient transition from the hospital environment to the home environment.

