#### **4.4 Exclusion criteria**

Preterm newborns will be excluded from the study if their gestational age at birth is equal to or greater than 34 weeks and 1 day, or if they have any of the following conditions: congenital malformations, chromosomal syndromes, active infections under treatment (with altered blood count or positive blood culture), neurological problems (such as grade III or IV intraventricular hemorrhage or brain malformations), neonatal asphyxia (with an Apgar score of less than 7 at the fifth minute), or congenital infections. Additionally, newborns will be excluded if they have any contraindications to performing the physiotherapy intervention protocol or the kangaroo position.

They will also be excluded if their parents or guardians do not consent to the newborn's participation in the study or request their withdrawal. If the newborn experiences adverse reactions to the physiotherapy protocol or kangaroo positioning, such as clinical instability during the procedure (e.g., cyanosis, crying, lethargy, signs of pain, generalized erythema) or in the short and medium term (e.g., worsening of the clinical condition, feeding intolerance, or behavioral disturbances), they will be excluded. Moreover, newborns may also be excluded if complications arise that prevent the application of the protocol, such as the need for invasive or non-invasive mechanical ventilation, oxygen therapy via a Hood Box, or the requirement of surgical procedures.

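### Section 5 declares the study free of risk, yet the same sentence and section 4.4 foresee cyanosis, bradycardia, apnoea and adverse reactions; no outcome counts these events, no reading falls within the handling, and infants who react are excluded

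*Protocol*

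**What the plan says.** Four places in the protocol bear on this.

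- **Section 5, Risks and Benefits.** It opens with "This study presents no physical or psychological risks to the newborn". The sentence then turns to what may be seen on handling, including "color fluctuations (paleness, perioral cyanosis, among others" and "cardiorespiratory changes (bradycardia, irregular breathing, apnea, irregular respiratory rate", as well as crying and irritability. The stated response is "If signs of overload are detected, the handling should be interrupted to allow the newborn to organize".
- **Section 4.4, Exclusion criteria.** It provides for exclusion after the start of the protocol: "If the newborn experiences adverse reactions to the physiotherapy protocol or kangaroo positioning, such as clinical instability during the procedure". Its examples include cyanosis, crying, lethargy and signs of pain, and later feeding intolerance or clinical deterioration.
- **Section 1, Introduction.** The hypothesis is that the combined protocol "will lead to an improvement in clinical outcomes while safely maintaining vital signs".
- **Sections 4.8.4.1 and 4.9.2.** Heart rate, respiratory rate, oxygen saturation, temperature and behavioural state "will be assessed at three-time points daily: I) immediately before the protocol (experimental or control), with the baby still in the incubator/crib", then 60 minutes into the kangaroo position, then 30 minutes later in the crib. The corresponding secondary outcome is "vital signs evaluated and recorded before and after the protocol (experimental and control) each day". Behavioural state and the Silverman-Andersen respiratory-distress score are also secondary outcomes.

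**The concern.** There are two linked problems. First, the risk statement is contradicted by the rest of its own sentence and by section 4.4. Calling the signs sensory overload does not make apnoea or bradycardia anything other than a physical event.

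Second, the protocol sets up no count of the events it foresees. The handling is the only planned difference between the arms, so a safety comparison should be able to see what happens during it. Followed as written, the vital-sign comparison would rest on readings taken before and well after the handling, in infants who tolerated it well enough to stay in the study. A transient event during handling could leave no trace in the outcome data, and an infant with a lasting reaction could leave the data set. At stake is the safety half of the stated hypothesis.

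**Working it through.** No figure in the protocol is in dispute, so the check sets the passages side by side.

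**Step 1. Is the no-risk statement consistent with the rest?** Section 5 foresees perioral cyanosis, bradycardia and apnoea on handling. Section 4.4 foresees adverse reactions to the physiotherapy or the kangaroo position. Either passage alone contradicts an absolute statement of no physical risk.

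**Step 2. When are the readings taken relative to the handling?** Section 4.8.5.1 gives 15 minutes of handling, followed at once by 60 minutes of kangaroo position. With time zero at the start of handling in the experimental arm, the schedule in section 4.8.4.1 gives:

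| Event | Minutes from start |
|---|---|
| Reading I, before the protocol | 0 |
| Handling | 0 to 15 |
| Kangaroo position starts | 15 |
| Reading II | 15 + 60 = 75 |
| Reading III | 75 + 30 = 105 |

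No reading falls inside the handling, and the first one after it comes 75 − 15 = 60 minutes after it ends.

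The respiratory-distress score does not fill the gap. Section 4.8.4.1 schedules it on Day 1 before the protocol and on Day 15 after it. Section 4.9.2 says it is obtained on each protocol day but gives no time of day. These two also need to be reconciled, but neither places a score within the handling.

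**Step 3. Does any outcome count the events?** Section 4.9 lists 2 primary and 7 secondary outcomes, 9 in all. None is a count or rate of overload signs, interrupted sessions, adverse reactions or safety exclusions. The data-collection sections (4.8.4 and 4.8.4.1) schedule no record of them either.

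**Step 4. What follows when a sign occurs?** Cyanosis and crying appear in both lists. Under section 4.4 the infant is excluded; under section 5 the handling is interrupted so that the infant can recover. The protocol does not say which applies when, so who remains in the comparison is not fixed.

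**Step 5. What does exclusion do to the comparison?** Each group has 17 infants (section 4.2), so each exclusion removes 1/17 = 5.9% of an arm, and two remove 2/17 = 11.8%. Both arms can lose infants who react to the kangaroo position, but only the experimental arm can lose infants who react to the handling. If such reactions occur, the infants lost are those who tolerated it worst, and the remaining vital-sign data look safer than the experience of all randomised infants. The protocol gives no expected reaction rate, so the size of this bias cannot be computed.

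**The case against.** The strongest reply is that the protocol does measure safety. Vital signs and behavioural state are taken three times a day in both arms. Respiratory distress is also a secondary outcome, and section 4.10 plans between-group tests. Crying is one of the behavioural states, so one of the listed signs is partly captured. This stands: a reader might infer that the trial measures no safety or that its hypothesis has no data behind it, and the documents do not support that.

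Other stronger readings also fail.

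- **That the handling is shown to be unsafe.** A protocol cannot show this. It shows only that the absolute statement is contradicted.
- **That section 5 calls the combined intervention safe.** It uses that word of the kangaroo position, which both arms receive.
- **That parents are misinformed.** The consent pages are not part of the reviewed text, and section 5 itself goes on to list the signs.
- **That the protocol promises to demonstrate absence of risk.** It asserts this as a premise and nowhere sets it as a result to be shown.
- **That the size of the defect is the upper limit left by zero events.** With 17 infants the one-sided 95% limit is 1 − 0.05^(1/17) = 16.2%. The arithmetic is right, but the limit follows from the sample size and would be the same after the fix.

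Two further replies have some force. Events may appear in the medical, nursing and physiotherapy records on which section 4.8.4 draws, and details of tabulation may sit in an analysis plan that is not shown. Neither removes the point: an analysis plan cannot recover events that the protocol does not have recorded systematically in both arms.

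**Conclusion.** The point holds in limited form. The no-risk statement is wrong on the protocol's own text. Safety is measured only by scheduled readings: none of the three daily readings falls within the handling, and none of the nine outcomes counts the foreseen events. The exclusion rule can also tilt the vital-sign comparison towards apparent safety.

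The direction of that bias rests on two assumptions: that some infants react to the handling, and that an excluded infant contributes no further readings. The protocol does not say whether readings taken before exclusion are kept; keeping them would lessen the bias without removing it. No exclusion for reaction in either arm would mean no such bias, but without a count by arm a reader could not tell. Neither primary outcome's definition nor its planned test is affected, so this should be corrected but does not by itself undermine the main analysis.

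**What to change.** 1. In section 5, replace the opening statement with one saying that the handling carries the risks listed there.
2. Reconcile sections 4.4 and 5 on what follows when the listed signs occur, so that interruption and exclusion are told apart. Which rule is right is for the clinical team.
3. Add to section 4.9.2 a descriptive safety outcome: the number of infants and the number of sessions with any listed overload sign, interruption, adverse reaction or safety exclusion. Record it at every session in both arms and report it by arm for all randomised infants, including those later excluded. The record should cover the handling itself and state the period observed in each arm, because section 4.8.3 (Control protocol) gives no length for the control infants' time in the crib, and an arm watched for longer will show more events.

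The cost is a short entry at each session, one descriptive table and a slightly less favourable stated risk profile. The sample size and the primary analyses do not change.
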